**Methods and design:**

A double-blind, randomized, double-masked, placebo-controlled clinical trial, including 620 patients from endemic areas for Leishmaniasis in Colombia was designed to investigate whether this patch is as effective as meglumine antimoniate for the treatment of cutaneous leishmaniasis but with less adverse events. Subjects with ulcers characteristic of cutaneous leishmaniasis will be medically evaluated and laboratory tests and parasitological confirmation performed. After checking the inclusion/exclusion criteria, the patients will be randomly assigned to one of two groups. During 20 days Group 1 will receive simultaneously meglumine antimoniate and placebo of nitric oxide patches while Group 2 will receive placebo of meglumine antimoniate and active nitric oxide patches. During the treatment visits, the medications will be daily administered and the presence of adverse events assessed. During the follow-up, the research group will visit the patients at days 21, 45, 90 and 180. The healing process of the ulcer, the health of the participants, recidivisms and/or reinfection will also be assessed. The evolution of the ulcers will be photographically registered. In case that the effectiveness of the patches is demonstrated, a novel and safe therapeutic alternative for one of the most important public health problems in many countries will be available to patients.

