
Nevertheless, due to the unstable nitric oxide release, the cream had to be applied frequently (4 times a day) making the adherence to the treatment difficult [39]. In Syria, another group used potassium nitrate acidified with salicylic acid and ascorbic acid for the topical treatment of *L. tropica *[40]. *In vitro*, this NO generating mixture destroyed the amastigotes and promastigotes of *Leishmania*; however, *in vivo*, the study of 40 patients presented inconsistent results, reducing the size of the ulcer in 28% of the subjects and healing only 12%. The discrepancy in these results is believed to be due to the technique used to obtain the NO. The acidification of nitrite produces an instant blast of NO, but its release is not maintained over a long period of time[40]. The difficulty of controlling the liberation of NO has created the necessity of looking for new techniques to regulate its release. The nanofiber polymers produced by the electrospinning technique have been studied in order to guarantee the constant release of pharmaceuticals on the lesion. In the electrospinning process, a high voltage is used to create an electrically charged jet of polymer solution, which dries and solidifies to leave behind a dry polymer fiber [41]. As this jet travels through the air, the solvent evaporates leaving behind a charged fiber that can be electrically deflected and collected on a metal screen [42,43]. Fibers with a variety of cross sectional shapes and sizes are produced from different polymers. With this technique, the encapsulation or entrapment of several pharmaceuticals, enzymes and proteins has been successful. In a previous study, nanofiber patches were successfully used as releasing vehicles of tetracycline hydrochloride. The release of tetracycline was constant for a period of 5 days [41,43]. Using the same model, a multilayer transdermal patch has been produced, in which nitrite is bound to an ion exchange resin (DOWEX) and electrospun into a polyurethane nanofibers layer. A solution containing Waterlock^® ^superabsorbent and polyurethane is electrospun on top of the nitrite-DOWEX layer. The ascorbic acid entrapped in the polyurethane solution is electrospun onto a third layer, with another layer of Waterlock^® ^superabsorbent and polyurethane as the fourth and final one. Upon hydration, this Nitric Oxide Releasing Patch (NOP) produces a stable release of 3.5 μmol of NO during 12 hrs [41,44,45]. In a pilot study, developed in Landazuri, Santander, Colombia, a placebo-controlled clinical trial was conducted with 35 patients who presented 68 ulcers produced by *L. panamensis*. Using the NOP, a 65% improvement was observed in the treated ulcers, with only a 25% improvement in the placebo group (p = 0.001). In this pilot study the unique adverse event described was pruritus in the area where the patch was applied (unpublished data). Taking into account the wide distribution of CL, the changes in its form of transmission and the difficulty related with the availability of medication, this study proposes to investigate whether the NO donor transdermal patch, produced by electrospinning is, at least, as effective as the meglumine antimoniate for the treatment of CL, with less adverse events and a lower cost, constituting therefore an effective therapeutic alternative. In case that the effectiveness of the NOP is demonstrated in this study, a novel and safe therapeutic alternative of easy access and higher adherence for one of the most important public health problems in our country will be made available.

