### Sample size

The sample was calculated according to the arccosine formula using a power of 80% and a type 1 error of 0.05%. Assigning a successful rate of 85% for meglumine antimoniate and 75% for NOP, 558 patients will be needed. After adjustment for a loss rate of 5%, the total of patients that must be recruited is 620 (310 patients per treatment group).

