### Data analysis phase

This phase will last 6 months. After completing all the data entry to the CFR, the results will be audited and the detected errors evaluated and corrected by the person in charge. The information will be entered in two different databases by two different people and the records will be compared to detect any discrepancy. The original CFR will be used to correct any mistake in the database.

For the statistical analysis, Stata 8.0 will be used. The descriptive analysis will be composed of medians and proportions according to the nature of the variables, with its respective 95% confidence intervals. As a dispersion measurement the standard deviation will be calculated. The distribution of the variables will be studied using the Shapiro-Wilk test. To detect any difference between the groups, a T-test or a Wilcoxon test will be performed according to its distribution. The categorical variables will be compared using the Chi2 test or the exact Fisher's test. If required, a model of multiple logistic regressions or a covariance analysis will be done.

Two interim analyses will be performed when 35% and 70% of the calculated sample is collected, with the objective of determining the differences in effectiveness and safety between the treatments.

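### The stated question is non-inferiority, but the trial is sized and tested for a difference, so short of superiority the plan cannot validly conclude that the patch is as effective as antimony

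*Protocol article*

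**What the plan says.** **Question.** The Background proposes to find out whether the patch "is, at least, as effective as the meglumine antimoniate for the treatment of CL, with less adverse events". The abstract (Methods and design) describes the trial as designed "to investigate whether this patch is as effective as meglumine antimoniate for the treatment of cutaneous leishmaniasis but with less adverse events". The Objectives are more neutral: they evaluate effectiveness, safety and healing rate in comparison with meglumine antimoniate, without saying what result is sought.

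**Sizing.** In the Sample size section, "The sample was calculated according to the arccosine formula", "using a power of 80% and a type 1 error of 0.05" (printed with a per cent sign and no sidedness). It continues: "Assigning a successful rate of 85% for meglumine antimoniate and 75% for NOP, 558 patients will be needed". No margin appears.

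**Analysis.** The Data analysis phase states: "To detect any difference between the groups, a T-test or a Wilcoxon test will be performed according to its distribution". It then states: "The categorical variables will be compared using the Chi2 test", with Fisher's exact test as the alternative. Success under Endpoints is a yes/no outcome, so the Chi2 or Fisher test is the one that applies to it. The 95% confidence intervals belong to the descriptive analysis. The two interim analyses are also aimed at finding differences. No section says what result would establish that the patch is as effective.

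**The concern.** A difference test takes equality as its null hypothesis. It can show that the patch is worse or that it is better. It cannot show that the patch is about as good, because failing to reject equality is also what an imprecise trial of a moderately worse treatment produces.

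The case for the patch, as the Background makes it, is comparable efficacy with fewer adverse events and lower cost. For that case the result that matters most is a patch that is similar or slightly worse, and this is where the plan has no decision rule. The planning scenario is itself a patch 10 points worse, in which the stated aim is not met.

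At stake is whether a treatment could be offered in place of one with a cure rate of about 85% on the strength of a test that never ruled out a material deficit. The Background foresees making the patch available if effectiveness is demonstrated.

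**Working it through.** **Inputs.** Success rates 85% (antimony) and 75% (patch), 80% power and 558 evaluable, i.e. 279 per arm, all from Sample size. Assumptions: type 1 error of 5% two-sided, since the printed 0.05% looks like a slip and sidedness is not given; normal approximation; no adjustment for the two interim looks.

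**1. Which kind of calculation gave 558?**
- Arcsine difference formula: n per arm = 2[(1.960 + 0.842)/(2·asin√0.85 − 2·asin√0.75)]² = 2(2.802/0.2518)² ≈ 248, total 496.
- Arcsine with continuity correction: 536. Fleiss: 500. Fleiss with continuity correction: 540.
- Non-inferiority, 85% in both arms, 10-point margin, one-sided 2.5%: n per arm = 2(0.85)(0.15)(7.849)/0.10² = 200.1, so 201, total 402 (316 at one-sided 5%).

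None gives exactly 558, but difference formulas come closest (540, a gap of 18) and the non-inferiority formula is far off. The figure was evidently planned for a difference.

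**2. How often is the difference test non-significant when the patch is worse?**
P(non-significant) = 1 − Φ[(δ − 1.96·SE₀)/SE₁], where SE₀ = √(2p̄(1−p̄)/279) and SE₁ = √{[0.85·0.15 + p(1−p)]/279}.

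| True patch rate | δ | SE₀ | SE₁ | P(non-significant) |
|---|---|---|---|---|
| 80% | 0.05 | 0.0322 | 0.0321 | 66% |
| 78% | 0.07 | 0.0329 | 0.0327 | 43% |
| 75% | 0.10 | 0.0339 | 0.0336 | 16% (15% if SE₁ is used throughout) |

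**3. What does a just-non-significant result still allow?**
Take an observed 85.0% versus 78.6%. The deficit is 0.064 and the pooled SE is 0.0327, so z = 1.959. The 95% interval uses the unpooled SE of 0.0326: 0.064 ± 1.96 × 0.0326, i.e. a deficit from about 0 to 12.8 points. This passes as no significant difference, yet it includes deficits larger than the 10 points the trial was sized to detect.

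**4. What would 558 evaluable patients deliver as non-inferiority?**
With 85% in both arms, SE = √(2·0.85·0.15/279) = 0.0302 and power = Φ(margin/SE − 1.96).

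| Margin (points) | Power with 558 | Total evaluable for 80% power |
|---|---|---|
| 10 | 91% | 402 |
| 8.5 | 80% | about 558 |
| 7.5 | 70% | 712 |
| 5 | 38% | 1602 |

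The smallest margin with 80% power is 2.802 × 0.0302 = 8.5 points. If the patch truly cures 75%, power at a 10-point margin is Φ[(0.10 − 0.10)/0.0336 − 1.96] = 2.5%, because the truth then lies on the margin.

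**The case against.** **The formal Objectives are neutral.** They ask for a comparison, and difference tests suit that. This is fair, and difference tests are also right for adverse events. But the Background and the abstract both state the purpose as showing the patch to be as effective, and the sizing and tests do not serve that purpose.

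**The article plans confidence intervals, and a statistical analysis plan may add a rule.** Estimation is indeed planned, and an interval for the difference could answer the question. As written, the intervals are descriptive and tied to no margin. The point rests on stated parts that do not fit together, not on detail left elsewhere.

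**Stronger readings that the text does not support.**
- A reader might infer that the plan will treat p > 0.05 as proof of equal efficacy. No section says so. The risk is that it could be read that way, since nothing else is offered for a similar result.
- A reader might take the 10-point gap as an implied margin. The 75% is given as the rate assigned to the patch, not as an acceptable loss.
- A reader might set the pilot's 65% against the 85%. The pilot figure is improvement among treated ulcers, not cure per patient, so it cannot stand in for the success rate.
- A reader might say that missing data and misclassification always favour the patch. Differential loss can act either way, and errors that dilute differences also favour a non-inferiority claim.

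**A margin rule is not a cure-all.** With a 10-point margin it would still declare non-inferiority about 34% of the time at a true 80% (Φ[0.05/0.0321 − 1.96]) and 15% at 78% (Φ[0.03/0.0327 − 1.96]). Those deficits lie inside such a margin, which is why the margin itself needs justification.

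**Conclusion.** The mismatch is real and lies in the article's own text. A clear superiority result would answer the question, and a significant deficit would answer it in the negative. For anything between, the plan has no valid way to conclude that the patch is as effective. If non-significance were taken for similarity, a patch truly 5 points worse would pass about two times in three, and one truly 10 points worse about one time in six.

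These figures rest on the assumptions listed with the inputs. At the literal 0.05%, non-significance at a true 75% would be about 70%, since Φ[(0.10 − 3.48 × 0.0339)/0.0336] gives about 30% power. This should be corrected before unblinding, because a margin chosen after the results are known carries little weight.

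**What to change.** 1. State the primary hypothesis for the success endpoint (Endpoints section) as non-inferiority on the difference in success proportions, patch minus antimony.
2. Fix a margin before unblinding and justify it on clinical grounds, not by relabelling the 10-point planning difference.
3. Declare non-inferiority only if the lower limit of the two-sided 95% confidence interval lies above minus the margin. Test superiority only after that.
4. Keep difference tests for adverse events.
5. State that a non-significant Chi2 test does not support a claim that the patch is as effective.
6. Rewrite the Sample size section with the margin, the assumed patch rate and the resulting power. An assumed 75% cannot stand beside a 10-point margin.

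**Cost.** The changes are to wording in the objectives, sample size and analysis sections. With 85% in both arms, no extra patients are needed for margins of about 8.5 points or more. Below that, either power under 80% is accepted or the trial grows: 712 evaluable at 7.5 points and 1602 at 5, which is 750 and 1687 recruited at the stated 5% loss (712/0.95 and 1602/0.95). The claim also becomes harder to obtain than a non-significant p-value.

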### Population

The population will be composed from two regions of Colombia. The first one is an endemic zone in Santander, Colombia, located between the Magdalena Valley and the East Mountain Range, which includes the municipalities of Landazuri, El Carmen, San Vicente, El Playon and Rionegro. The second region is an endemic zone in North Tolima, which includes the municipalities of Chaparral, San Antonio, Libano, Falan, Palocabildo and Mariquita.

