### Follow-up visits

This phase will last 10 months. During the follow-up, the patients will be seen by the research group in 4 opportunities. The first visit will take place the day after the end of the treatment (day 21) in which new blood samples will be taken for biochemical determinations. The second, third and fourth visits will be realized on day 45, 90 and 180 respectively. During these visits the healing process of the ulcer, the presence of recidivisms and/or reinfection and the health of the participants will be assessed. The evolution of the ulcers will be photographically registered.

The maximum and minimum diameters of the ulcer will be measured using a graduated ruler, and the induration using the ballpoint pen technique. The ulcer and induration areas will be calculated separately, and then registered in the CRF. The evaluation of the clinical response will be based on the ulcer showing the least improvement.

1. Complete clinical response: Complete reepithelization of the ulcer and disappearance of the induration.

2. Clinical Improvement: Reduction of more than 50% of the ulcer and the induration areas in relation to the last clinical evaluation.

3. Absence of clinical response: Increase or reduction of less than 50% of the ulcer and the induration areas in relation to the last clinical evaluation.

4. Therapeutic failure:

a. Increase in the size of the ulcer by more than 50% in relation to the last clinical evaluation

b. Presence of the ulcer three months after the beginning of the treatment.

c. Reactivation: Appearance of a lesion on the edge or in the center of the scar, with positive parasitological diagnosis, after a period of complete reepithelization.

d. Affection of the mucous membranes: Presence of affections of the mucous membranes during the treatment, at the end of it or in the follow-up visits.

5. Reinfection: Activation of an ulcer in an area different from the original lesion.

For subjects whose treatment will have been considered a failure the code will be broken and they will be remitted to their original health center to look for other therapeutic approach.

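### Adjusting for lesion number, ulcer size and region is left to an undefined condition; fixing one adjusted risk difference in advance would be a modest gain at almost no cost

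*Protocol article*

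**What the plan says.** Under Data analysis phase, the protocol article says: "The categorical variables will be compared using the Chi2 test or the exact Fisher's test". The next sentence reads: "If required, a model of multiple logistic regressions or a covariance analysis will be done". It does not say what would make the model necessary, or which result would then carry the conclusion. The Endpoints section defines success and failure, a binary outcome, so the Chi2/Fisher sentence applies to it by default. No sentence names a primary analysis of success.

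Three other places matter:

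- **Follow-up visits:** "The evaluation of the clinical response will be based on the ulcer showing the least improvement". Exclusion criterion 3 rules out only patients with more than five active lesions, so a participant may have one to five.
- **Population:** "The population will be composed from two regions of Colombia" (Santander and North Tolima).
- **Baseline data:** Table 1 and the Initial visit section have ulcers measured at day 0. Applying exclusion criterion 3 requires a count of current lesions. The Background lists number and size of lesions among the main considerations when treating the disease.

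Randomization is described as blocked, and no stratification factor is stated.

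**The concern.** Two things are at stake.

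The first is precision. If success requires the worst ulcer to heal, a patient with four ulcers has more chances to fail than a patient with one. A comparison that ignores lesion number then carries variation that could be removed with data already in hand.

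The second is an open choice. If the adjusted model may be run, and preferred, after the unadjusted result is known, the plan allows two answers to one question without saying which counts. An analysis plan that carried the sentence over unchanged would inherit the problem.

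**Working it through.** **Inputs from the Sample size section.** "Assigning a successful rate of 85% for meglumine antimoniate and 75% for NOP, 558 patients will be needed". That is 279 per arm, with 80% power. The type 1 error is printed as 0.05 followed by a percent sign; I read it as 5%, two-sided.

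**The plan's own figure.** On the angular scale, h = 2·asin(√0.85) − 2·asin(√0.75) = 2.346 − 2.094 = 0.252. Then n = 2·(1.960 + 0.842)²/h² = 247.6, so 248 per arm or 496 in total, not 558. With 279 per arm, power is Φ(h·√(279/2) − 1.96) = Φ(1.01), about 84%. The mismatch does not affect this point, and I use 279 per arm throughout.

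**Why lesion number should predict success.** Suppose each ulcer heals independently with probability q and all must heal. A patient with k ulcers then succeeds with probability qᵏ. Using 0.85 as a per-ulcer rate purely for illustration, k = 1 gives 0.85, k = 2 gives 0.85² = 0.72 and k = 5 gives 0.85⁵ = 0.44. At the other extreme, if all ulcers in a patient heal or fail together, success is 0.85 whatever k is, and lesion number carries no information. The documents do not say where the truth lies.

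**Gain from lesion number alone.** These are simulations at 279 per arm, 85% vs 75%, with every ulcer required to heal. Mean lesion count was set at 1.92 to 1.94; the pilot had "35 patients who presented 68 ulcers", and 68/35 = 1.94. The spread of counts is an assumption.

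| Healing of ulcers within a patient | Variance ratio, unadjusted/adjusted | Power, unadjusted to adjusted |
|---|---|---|
| Independent | 1.05 | 83.6% to 85.5% |
| Correlation 0.2 | 1.05 | 84.3% to 85.5% |
| Correlation 0.5 | about 1.00 | no material gain |

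A ratio of 1.05 is a reduction of 1 − 1/1.05 = 4.8%. A separate set of runs gave reductions of about 2 to 6% and power gains of 1 to 2.5 points.

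**A generic baseline covariate.** One standardised covariate, 4,000 trials per setting. The adjusted test is the Wald test of treatment in the logistic model. The covariate strengths are assumed, since the documents give none.

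| Log-OR per SD | Variance explained | Power unadjusted | Power adjusted | Type 1 error if either result may be claimed |
|---|---|---|---|---|
| 0 | 0% | 83.8% | 83.5% | 4.9% |
| 0.3 | 1% | 85.2% | 85.3% | 5.2% |
| 0.5 | 3% | 83.3% | 84.2% | 6.0% |
| 0.8 | 8% | 84.5% | 87.9% | 5.8% |
| 1.2 | 16% | 84.4% | 90.4% | 6.8% |

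Either analysis fixed in advance rejected in 4.5 to 5.3% of null trials. The Monte Carlo standard error at 5% is √(0.05·0.95/4000) = 0.3 points. If the covariates are also chosen freely, taking the best of eight models from three covariates (log-OR 0.5 or 0.8 each) gave 7.2% and 9.6%.

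**The case against.** The case against has real force.

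- **Validity.** An unadjusted comparison of two proportions is valid in a randomised trial and matches the sizing at 85% vs 75%. A reader might infer that the plan uses a wrong test or throws baseline data away. It does neither: the same paragraph provides for a regression model that could use those data.
- **Labelling.** A reader might take Chi2 to be the declared primary test. The sentence is generic, so this is an inference from the binary endpoint.
- **Detail left elsewhere.** Covariate lists and the ranking of analyses are commonly left to the statistical analysis plan, which is not shown. Their absence is therefore not the point. What stands is the conditional wording that the article does print, and the better method available from data it already collects.
- **Direction of the incentive.** The type 1 error figures assume that the analyst seeks significance. The Background aims to show that the patch is at least as effective as the comparator, so a non-significant difference could be the welcome result. Claiming a difference only when both tests are significant lowers type 1 error: one check (log-OR 0.7, 1,500 runs) gave 3.9%, against 4.9% unadjusted and 5.1% adjusted. This limits the inflation claim. The choice still has a cost in that direction: at log-OR 0.8 the chance that both tests detect the 10-point difference is 84.5 + 87.9 − 89.5 = 82.9%, below either test alone.
- **Data.** A reader might assume that ulcer duration is recorded. The text gives it only as an entry threshold of more than two weeks.

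**Conclusion.** The point holds as a free improvement of modest size. The stated test is not in error.

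Lesion number alone should cut the variance of the difference by about 0 to 6%. The top of that range is worth about 0.06 × 558 = 33 patients' information, and the bottom applies if ulcers in one patient heal together. Some clustering is plausible, since ulcers share a host and one treatment is systemic. Area and region would add to the gain if they are prognostic. Overall this means nothing to a few points of power, about 6 at the strongest covariate effect tried. A reader might infer a larger saving in patients, but that needs strong area and region effects that the documents do not give.

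Leaving the choice open could move type 1 error from 5% to about 5 to 7% with one covariate and a search for significance, and higher only if the covariates are also picked freely.

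The verdict assumes that the worst-ulcer rule in Follow-up visits governs the success endpoint, which the Endpoints section does not restate, and that Chi2/Fisher is its default test.

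**What to change.** Delete the condition 'If required' and name one primary analysis in advance. For example: the primary analysis is the difference in success proportions between groups with its 95% confidence interval, standardised from a logistic model with treatment, number of ulcers, baseline ulcer area and region; the Chi2 or Fisher test is supportive. Say in advance how area is defined for patients with several ulcers, for instance the largest ulcer on a log scale. Add ulcer duration only if the case report form records it.

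The model is small for the data: the planning rates imply 279 × 0.15 + 279 × 0.25 = about 112 failures for four terms.

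If the sponsor prefers the unadjusted comparison, it should be fixed as primary with the model as a named sensitivity analysis. That closes the open choice but gives up the precision.

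The cost is one sentence and a few lines of code. Number of ulcers, area and region need no new data, and the target stays the difference in proportions on which the trial was sized.
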